# Background

Preterm infants are at increased risk for the development of serious nosocomial infections, especially very low birth weight (VLBW) infants at a NICU.1 In a recent review of the literature, we found that the intestinal bacterial colonisation in preterm infants is much more diverse than in term infants and that antibiotics cause a significant delay in the intestinal bacterial colonisation.2 Breast milk has a bifidogenic effect on the intestinal bacterial flora.3,4 Furthermore, breastfed infants, especially term infants, have less infections and develop less atopy.5,6 Many factors have been implicated in this effect, including prebiotics. Addition of prebiotics to infant formula has been found to show potential advantageous effects in term and preterm infants.7,8 In breast milk, several types of oligosaccharides can be distinguished: acidic oligosaccharides (20%) and neutral oligosaccharides (80%). In the past, research has mainly focussed on neutral oligosaccharides such as galacto-oligosaccharides and fructo-oligosaccharides (GOS/FOS). As breastfeeding may have anti-inflammatory effects and is thought to prevent the development of atopy, the same potential effects have been attributed to prebiotics. So far, most studies have focussed on GOS/FOS supplementation. Supplementation of GOS/FOS results in:9,10

1. stimulation of a bifidogenic flora
2. reduction of pathogens in the intestine
3. production of beneficial fermentation metabolites such as short chain fatty acids (SCFA)
4. decrease of stool pH
5. improved intestinal physiology (stool characteristics, motility)

However, in breastfeeding only 80% of the oligosaccharides are neutral (as in GOS/FOS), whereas 20% are acidic. Acidic oligosaccharides (AOS) can be derived from carrots with their active component pectin. Pectin is a common structural component of all higher plants. Cooking of pectin-containing vegetables induces the cleavage of the long-chain pectin polymers into oligosaccharides. For already nearly 100 years, carrots are known to have health promoting effects. In 1908, carrot soup was used as treatment of diarrhoea.11 In 1997, Guggenbichler identified the anti-adhesive effect of acidic oligosaccharides.12

In preliminary studies, the combination of acidic and neutral oligosaccharides is more effective than neutral oligosaccharides alone. Preliminary studies indicate that supplementation of acidic oligosaccharides may have several advantageous effects.13

1. stimulating a bifidogenic flora
2. preventing adhesion of pathogens to epithelial tissues
3. stimulation of Th1 cytokine response (e.g. TNF-, IFN-gamma) and decreasing the Th2 cytokine release (e.g. IL-10, IL-4, IL-5)
4. improvement of the response to immunizations

As a result of these effects, it is thought that infants receiving a combination of GOS/FOS with AOS will have:

1. less infections
2. less feeding intolerance
3. less atopy later in life

As infections are still a major cause of morbidity and mortality, reducing the incidence of serious infections is very important. As controversy exist on the definitions for serious infections in neonates, we redefined in a previous study the CDC criteria for serious infections in neonates1 and found these criteria applicable in a study in preterm infants.14

In the current study, we want to determine the effect of enteral supplementation of acidic and neutral oligosaccharides on the incidence of serious infections, using the previously described criteria for serious infections in preterm infants at high risk for serious infections, with a gestational age < 32 weeks and/or a birthweight < 1500g.

In conclusion, this double-blind randomised controlled trial has the following aims:

1. To determine the effect of acidic and neutral oligosaccharides supplemented enteral nutrition on infectious morbidity, intestinal microflora, feeding tolerance, and short-term outcome in VLBW infants.
2. To elucidate the role of acidic oligosaccharides in modulation of the immune response and postnatal adaptation of the gut.
3. To determine the long term effects of acidic and neutral oligosaccharides supplemented enteral nutrition in the neonatal period on the development of allergic and infectious disease in the first years of life (by questionnaire) and neurodevelopmental outcome, neuromotor development at the corrected age of 1 and 2 years and mental/motor development (BSIDII) at the corrected age of 2 years (as part of the regular follow-up of NICU infants).
4. To determine the effect of acidic and neutral oligosaccharides supplemented enteral nutrition on the response to immunizations with Diphteria-Tetanus-acellular pertussis - inactivated polio - *Haemophilus influenzae* type B – Pneumococcus (DTaP-IPV-HIB-Pneu) vaccination (initial 3 doses), and booster vaccination (4th dose). In infants with parents from endemic Hepatitis B parts of the world and in infants born to Hepatitis B positive mothers, the response to immunization with Hepatitis B vaccin will also be evaluated.

**Methods**

The study is designed as a double-blind randomised clinical trial. Approval of the study protocol by the medical ethical review board of VU University Medical Center Amsterdam will be obtained before the start of the study.

## Study population

Infants with a gestational age <32 weeks and/or birth weight <1500 g admitted to the level III neonatal intensive care unit (NICU) of the VU University Medical Center, Amsterdam, are eligible for participation in the study. Written informed consent is obtained from all parents.

Exclusion criteria are: major congenital or chromosomal anomalies, death <48 h after birth, transfer to another hospital <48 h after birth and admission from an extraregional hospital.

## Treatment allocation and blinding

To balance birth weight distribution into treatment groups, each infant is stratified to one of three birth weight groups (<799 g, 800-1199 g, ≥1200 g) and randomly allocated to treatment <48 hours after birth. An independent researcher uses a computer-generated randomisation table based on blocks of four (provided by Nutricia Nederland BV, Zoetermeer, The Netherlands) to assign infants to treatment A or B, which correspond to batch numbers on the nutrition products. Investigators, parents, medical and nursing staff are unaware of treatment allocation. The code for the batch numbers is broken after data analysis is performed.

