**Treatment**

Acidic and neutral oligosaccharides powder and the control powder (maltodextrin) are prepared by Numico Research (Friedrichsdorf Germany) and are sterile packed. During the study period, acidic and neutral oligosaccharides and control powder are monitored for stability and microbiological contamination.

Between days 3 and 30 of life, acidic and neutral oligosaccharides supplementation (20%/80% mixture) is administered in a dose of maximal 1.5g/kg/day to breastfeeding or preterm formula in the intervention group. Two members of the nursing staff daily add supplementation to breast milk or to preterm formula (Nenatal Start®, Nutricia Nederland B.V., Zoetermeer, The Netherlands), according to the parents’ choice. Per 100 ml, Nenatal Start® provides 80 kcal, 2.4g protein (casein-whey protein ratio 40:60), 4.4g fat and 7.8g carbohydrate. When infants are transferred to other hospitals before the end of the study, the protocol is continued under supervision of the principal investigator (IW).

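### Two shared product codes (A/B) combined with fixed blocks of four leave about a third of codes predictable to someone tracking a stratum, and tie every infant's masking to one letter

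*Protocol*

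**What the plan says.** All of the allocation rules stand in the Protocol, section Treatment allocation and blinding.

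- Generation: "An independent researcher uses a computer-generated randomisation table based on blocks of four". Randomisation is stratified by three birth weight groups.
- Labelling: the table serves "to assign infants to treatment A or B, which correspond to batch numbers on the nutrition products". The number of batch numbers per arm is not given.
- Masking: "Investigators, parents, medical and nursing staff are unaware of treatment allocation".
- Code break: "The code for the batch numbers is broken after data analysis is performed". Which analysis is meant is not spelled out.

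The section Study population names one recruiting NICU. Under Treatment, "Two members of the nursing staff daily add supplementation to breast milk or to preterm formula", so coded product is handled on the ward every day. The protocol describes no infant-specific numbering, no variation in block size, and no step that keeps block size or the sequence of codes from the ward.

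**The concern.** Two features that are acceptable singly become weaker in combination.

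**Predictability.** In a fixed block of four, the last code always follows from the first three, and the third follows when the first two match. Keeping the list with an independent researcher does not prevent this inference, because it uses codes already in use on the ward.

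**Pooling of impressions.** When infants share a letter, observations about them accumulate by letter. The Background lists stool characteristics, stool pH and motility among the effects of neutral oligosaccharides, and the trial itself measures faecal pH, viscosity and transit time. If the unit settles on an opinion about one letter, that opinion applies to a whole arm at once, whether or not it is correct.

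Some outcomes depend on decisions made on the ward. Sepsis requires a positive blood culture, so someone must first decide to take one. The masked investigators who classify infections cannot recover a culture that was never taken. Under Nutritional support, the medical staff have the final say on advancing feeds, which bears on the feeding tolerance outcomes in Table 1. The follow-up also includes parent questionnaires.

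**Working it through.** **Inputs from the Protocol.** Block size 4, two arms, three strata (Treatment allocation and blinding); 2 × 54 infants (Sample size).

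**The plan's own figure.** The protocol states no predictability figure. Its sample size is used here only for scale, and it reproduces: 2 × 7.85 × 0.63 × 0.37 / 0.26² = 3.660 / 0.0676 = 54.1 per arm, so 108 infants in total.

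**Codes that are certain in advance.** A block with two A and two B has six equally likely orders: AABB, ABAB, ABBA, BAAB, BABA, BBAA.

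- Positions 1 and 2 are never determined.
- Position 3 is determined when the first two codes match (AABB, BBAA): 2 of 6.
- Position 4 is always determined: 6 of 6.
- Total: (2 + 6) / (6 × 4) = 8/24 = 33.3%.

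**Best guess.** The observer always guesses the letter with more places left in the block.

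| Position | Probability correct |
|---|---|
| 1 | 1/2 |
| 2 | 2/3 |
| 3 | 1/3 × 1 + 2/3 × 1/2 = 2/3 |
| 4 | 1 |

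Mean: (1/2 + 2/3 + 2/3 + 1) / 4 = 17/24 = 70.8%, against 50% by chance.

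**Scale in this trial.** If all blocks were complete, 108 × 1/3 = 36 codes would be certain. The protocol does not give the split across strata, so three splits were assumed (equal thirds; 20/40/40%; 10/30/60%) and simulated with incomplete last blocks. Each gave about 35 of 108 (32%), so the result hardly depends on the split.

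**Alternatives, same measure.**

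| Design | Codes certain in advance |
|---|---|
| Fixed blocks of 4 (as planned) | 33% |
| Fixed blocks of 6 | 25% |
| Fixed blocks of 8 | 20% |
| Random blocks of 4 or 6, boundaries hidden | about 6% (simulated, 36 infants per stratum) |

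**Reach of one correct identification.** If each arm has a single code, correctly identifying one infant's product decodes that letter and, by elimination, the other: up to 107 further infants. With infant-specific numbers and no A/B list on the ward, it exposes none.

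**The case against.** The strongest reply is that these percentages describe an observer with perfect records. Prediction needs the block size and the ordered codes of the earlier infants in the current block of the same stratum. Three strata run side by side, infants may be transferred during treatment, and a nurse adding powder sees that infant's product, not the stratum's sequence. The protocol does not say that ward staff know the block size. This stands: a reader might infer that a third of allocations are certain to anyone at the cotside, and the documents do not support that.

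Second, what becomes predictable is a letter. It gives no basis for selective enrolment unless the letter has already been decoded, and allocation within 48 hours of birth limits delay. This also stands.

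Third, a reader might infer that one guess unblinds the trial. It does not: a wrong guess mislabels every infant, stool changes are a group-level effect, and feeding varies between breast milk and formula. Nothing says that the powders can be told apart. Several batch numbers per arm are also possible, although a ward list linking them to A or B would have the same effect as a single code. What remains is the pooling: a shared opinion, even a wrong one, acts on one arm as a whole.

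Fourth, a reader might infer that the code is opened after the 30-day results, exposing later assessors and parents. The protocol states no such opening, and Statistical analysis includes the neuromotor and mental/motor outcomes. The sentence can fairly be read as keeping the code closed until those are analysed, so only a request for clarity remains.

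Finally, infections are classified by two masked investigators. That protects classification, but not the earlier decision to culture. The size of any effect there cannot be quantified from the documents.

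**Conclusion.** The concern holds in conditional form. With fixed blocks of four and shared A/B codes, someone who knows the block size and follows a stratum could know about a third of codes in advance (8/24, or about 35 of 108 infants) and guess correctly 71% of the time. The assumptions are knowledge of the block size and of the order and codes of earlier infants in the stratum. The further step to active versus control needs a correct identification of one product. Its reach to the whole trial assumes one code per arm, or a list on the ward linking batch numbers to letters.

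Nothing in the protocol shows that masking has failed or that the primary comparison is biased. The labelling and block size are nevertheless stated design choices, not detail left for later, and a better arrangement is available at little cost. The timing of the code break is a minor clarification.

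**What to change.** 1. Replace the shared A/B product codes with infant-specific pack numbers. The independent researcher alone holds the link to arm, and no A/B list is kept on the ward. Several codes per arm would help less, because a list linking them to the letters would undo the gain.
2. Use randomly varying block sizes within stratum, and do not disclose the sizes to site staff. This reduces certainty but does not remove all advantage in guessing.
3. State that the analysis named in the code-break sentence includes the 2-year follow-up, or that the code stays closed to parents and assessors until those assessments are complete.

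The cost is extra labelling by the manufacturer, a regenerated list and a slightly larger possible imbalance within a stratum. No additional infants are needed. If product is already labelled, the third change can still be made.

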**Treatment**

Acidic and neutral oligosaccharides powder and the control powder (maltodextrin) are prepared by Numico Research (Friedrichsdorf Germany) and are sterile packed. During the study period, acidic and neutral oligosaccharides and control powder are monitored for stability and microbiological contamination.

Between days 3 and 30 of life, acidic and neutral oligosaccharides supplementation (20%/80% mixture) is administered in a dose of maximal 1.5g/kg/day to breastfeeding or preterm formula in the intervention group. Two members of the nursing staff daily add supplementation to breast milk or to preterm formula (Nenatal Start®, Nutricia Nederland B.V., Zoetermeer, The Netherlands), according to the parents’ choice. Per 100 ml, Nenatal Start® provides 80 kcal, 2.4g protein (casein-whey protein ratio 40:60), 4.4g fat and 7.8g carbohydrate. When infants are transferred to other hospitals before the end of the study, the protocol is continued under supervision of the principal investigator (IW).

## Nutritional support

Protocol guidelines for the introduction of parenteral and enteral nutrition follow current practice at our NICU. Administration of parenteral nutrition starts at day 1 and will be advanced gradually until amino-acid intake reaches 3 g/kg/day at day 6. Parenteral nutrition is discontinued when enteral feeding reaches a volume of approximately 150 mL/kg/day or less in case of fluid restriction. Parenteral nutrition, an all-in-one mixture provided by the hospital pharmacy, contains per 100 mL 54 kcal, 8.5 g glucose, 1.7 g amino acids and 1.7 g lipids. If necessary, glucose, amino acids and lipids will be given in separate solutions. Full enteral feeding is defined as >120mLkg/day enteral feeding as some infants have fluid restriction.

Guidelines for the introduction of enteral nutrition are as follows: 1. Minimal enteral nutrition (breastfeeding or preterm formula (Nenatal Start®) starts at day 1 (6-12 mL daily); 2. Enteral nutrition is advanced either from day 2 or from day 3-4 in case of: BW <p10, GA <26 weeks, Apgar score at 5 minutes <6, pH <7.10 and/or base deficit >10 mmol/L in arterial cord blood; 3. Feeding is advanced at a dose of 15-20 mL/kg/day to a maximum of 150 mL/kg/day (based on actual weight). Furthermore, guidelines for reduction/withholding of enteral feeding are: 1. Enteral feeding is reduced/withheld in case of gastric residuals (> total volume of past 2 feedings), bilious residuals, emesis, ileus or necrotising enterocolitis Bell’s stage ≥II;15 2. When signs of feeding intolerance resolve, feeding is advanced in the volume given before reduction/withholding within 2 days.

For each infant in the study a feeding schedule is proposed, based on birth weight and the guidelines as mentioned above. However, the medical staff of our NICU has final responsibility for the administration of parenteral nutrition and advancement of enteral feeding.

**Study outcome measures**

##### Study outcome measures

Primary outcome of the study is the effect of acidic and neutral oligosaccharides (20%/80% mixture) supplemented enteral feeding in a maximum doze of 1.5g/kg/day on infectious morbidity as previously defined.1,14 Furthermore, parameters of feeding tolerance, and short-term outcome are evaluated (Table 1). In addition to clinical outcome, intestinal permeability, faecal flora (including pH, viscosity measurements and acetate measurements), faecal IL-8 and calprotectin (Diagnostic Products Corporation Nederland BV), gastrointestinal transport time (by carmine red) and plasma cytokine concentrations (Il-2, Il-4, IL-5, IL-8, IL-10, TGFα , IFNγ,) are determined during the 30 day study period (Table 2).

*Clinical outcome measures*

The following perinatal characteristics are registered to assess prognostic similarity: maternal age and race, obstetric diagnosis, administration of antenatal steroids and antibiotics, mode of delivery, sex, gestational age, birth weight, birth weight <p10, Apgar scores, pH of the umbilical artery, clinical risk index for babies16 and administration of surfactant.

During the study period actual intake of enteral and parenteral nutrition, powder supplementation and type of feeding (breast milk or preterm formula) are recorded daily.

The occurrence of serious infections is determined by two investigators, unaware of treatment allocation, as previously described.1,14 Serious infections include sepsis, pneumonia and meningitis. In addition, the presence of pyelonephritis, and arthritis are recorded. Sepsis work-up consists of blood, cerebrospinal fluid and urine (suprapubic bladder tap) culture. Sepsis is defined as the combination of a positive blood culture and the presence of at least two clinical signs (body temperature <36.5°C or >37.5°C, hypotension, tachycardia, apnoeic attacks, feeding problems, irritability or apathy). Meningitis is diagnosed when micro-organisms are cultured in the cerebrospinal fluid. Pyelonephritis is diagnosed when both urine culture and dimercaptosuccinic acid (DMSA) renal scan are positive. Pneumonia is defined as the combination of a positive culture of tracheal aspirate, bronchial secretion or sputum and the presence of at least one clinical sign in ventilated infants (purulent sputum, changed sputum characteristics or deterioration of ventilation settings) or at least two clinical signs in non-ventilated infants (tachypnea, cyanosis, wheezing/rales/crepitations or purulent sputum/changed sputum characteristics). Arthritis is defined as the combination of a positive culture of intra-articular fluid and the presence of signs of articular inflammation.

*Postnatal adaptation of the gut*

The effect of acidic and neutral oligosaccharides supplemented enteral nutrition on postnatal adaptation of the gut is studied by measuring intestinal permeability and by determining intestinal microflora.

Intestinal permeability is measured by the sugar absorption test, as previously described.17 After instillation of the test solution, 2 ml/kg by nasogastric tube, urine is collected for 6 hours. After collection, 0.1 ml chlorohexidine digluconate 20% (preservative) is added to the urine and samples are stored at -20oC until analysis. Lactulose and mannitol concentrations (mmol/mol creatinine) are measured by gas chromatography as previously described.18 The lactulose/mannitol ratio is calculated and used as a measure of intestinal permeability.

Faecal samples are stored at -20oC until analysis by fluorescent in situ hybridisation (FISH) using specific 16S rDNA-targeted probes as described by Harmsen et al.3 gastrointestinal transit time (GGT) will be measured by adding 20 mg carmine red to 1 feeding. GGT is defined as the time from feeding the marker to its appearance in the diaper.19 Stool pH will be measured using a Handy lab pH meter.20

*Immune response*

The effect of acidic and neutral oligosaccharide supplemented enteral nutrition on the immune response is investigated by determining the development of the immune response to Diphteria - Tetanus – acellular Pertussis - inactivated Polio-Haemophilus influenza type B - Pneumococcus (DTaP-IPV-HiB-Pneu) immunizations (first 3 doses), and if indicated Hepatitis B vaccin, and the development of the memory function of the immune response to these immunizations by measuring the response to the 4th booster dose. In addition, the plasma cytokine concentrations (Il-2, Il-4, IL-5, Il-8, IL-10, TGF α, IFN γ), faecal calprotectin and IL-8 concentrations will be measured.

*Follow-up*

To investigate neurodevelopmental outcome, neuromotor development at the corrected age of 1 and 2 years21 and mental/motor development (BSIDII) at the corrected age of 2 years are assessed.22

To determine the incidence of allergic and infectious disease in the first year of life, faecal samples (FISH, calprotectin and IL-8) and IgE/IgG4 levels will be measured at 5 and 12 months and questionnaires will be sent to the parents prior to the follow-up visit at the corrected age of one year.

To determine the frequency of side-effects of immunizations, questionnaires will be given to the parents at the time of immunizations.23

**Sample size**

Based on the differences (76% and 50% respectively) in infectious morbidity in the GEEF study,14 and a two-tailed α=0.05, β=0.20, a sample size of 2 x [2*7.85*0.63(0,37)]/(0,26)2 = 2 x 54 infants was calculated.

